### Design and Randomization

The stepped-wedge cluster design accounts for the proportion of the study period that each group spends in the control and intervention periods (Table 1).

Randomization will occur at the unit level. There are 2 units at HUP-Cedar; using a random number generator, the first unit will be chosen. Eight weeks later, the second unit will begin Thrive referrals. Each unit has 1 case manager and 1 social worker responsible for discharge planning and initiating Thrive referrals. Due to the small number of clinicians and their shared workspace, all 4 will be trained simultaneously, and concealing allocation will not be feasible.

**Table 1 table1:** Study diagram for the type I hybrid effectiveness-implementation, stepped-wedge, cluster randomized controlled trial of the adapted Thrive clinical pathway for serious mental illness.

Cluster	Baseline (3 months)	Enrollment period 1 (two months)	Enrollment period 2 (two months)	Follow-up (17 months)
Sequence 1 (first unit)		✓	✓	✓
Sequence 2 (second unit)			✓	✓

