### Variables and Measures

The primary independent variable is participation in Thrive. The outcome variables include Thrive referral rates; 30-, 60-, and 90-day readmissions and ED visits; and receipt of primary and specialty care within 30 days of index hospitalization [23-25]. For Thrive participants, these outcomes will be assessed from the date of hospitalization that resulted in a referral to Thrive. For the usual care group, we will identify all readmission and ED visits occurring after the first index hospitalization identified in the EHR from the calendar year of the study. Additional covariate data at both the patient (eg, demographics, comorbidities, or mental health diagnoses) and unit levels (eg, type of unit, discharging team, or provider) will be collected.

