### Analysis

Monthly reports will be generated to monitor referral patterns to the Thrive clinical pathway. The primary analysis will use a mixed-effects negative binomial regression model, accounting for both medical team and time effects, to evaluate readmission and ED utilization patterns comparing those with and without SMI who receive Thrive to those with and without SMI who receive usual care [26,27]. Sensitivity analyses may include logistic regression, depending on data distribution.

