### Power Analysis

Based on a power analysis, a sample size of 472 (236 Thrive participants and 236 usual care) for the outcome of readmissions, or a sample of 534 (267 Thrive participants and 267 usual care) for the outcome of ED visits, will yield 80% power to detect significance at the *P*<.05 level. Our goal is a sample size of 534 to ensure adequate power for both outcomes. This assumes a 20% (106/534) loss to follow-up rate. Furthermore, assuming at least a third of the patients will have SMI and an overall 30-day readmission rate of 28% (44/160), a sample of 534 patients will have 80% power to detect an odds ratio as small as 1.46, comparing those with and without SMI, to be statistically significant at the *P*<.05 level. Power analyses were conducted using Power Analysis and Sample Size 2021 (NCSS Statistical Software) [28].

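### The primary model names medical team and time but not the randomised hospital unit, so a pre-existing difference between the two units can bias the Thrive effect

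*Protocol article*

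**What the plan says.** Protocol article, Design and Randomization, fixes what is randomised: "Randomization will occur at the unit level". Only a pair of clusters exists, and chance settles which one goes first; the other follows after a fixed delay: "Eight weeks later, the second unit will begin Thrive referrals". Table 1 gives a 3-month baseline, two enrollment periods of 2 months each and 17 months of follow-up. The two units differ in Thrive status only in enrollment period 1.

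Aim-2 Analysis: the primary analysis is a "mixed-effects negative binomial regression model, accounting for both medical team and time effects". No section says that hospital unit enters this model.

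Variables and Measures: covariate data at the patient and "unit levels (eg, type of unit, discharging team, or provider) will be collected", but these are not assigned to the primary model. The same section states: "The primary independent variable is participation in Thrive".

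The article does not say whether teams are nested in units or cross them, whether team is a fixed or a random effect, or how time is coded.

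**The concern.** The article names a clustering factor for the primary model, and it is not the factor that was randomised. In a stepped wedge, the cluster effect is what lets each cluster serve as its own control. Without it, any comparison of the two units while they are in different states mixes the Thrive effect with whatever already distinguished them, such as case mix or staffing. With many clusters randomisation would even this out on average. Here a single random choice between two units decides the order, so no balance can be expected. A persistent difference in readmission or ED use between the units could then be reported as benefit or harm of Thrive.

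**Working it through.** **Stated figures.** The point challenges no number in the protocol. The totals of 472 and 534 cannot be rebuilt, because Power Analysis gives no Thrive-versus-usual-care effect size. The 534 total, "534 (267 Thrive participants and 267 usual care) for the outcome of ED visits", is used below only to set accrual.

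**Inputs.** From Table 1: 3 + 2 + 2 + 17 = 24 months and 2 units, so 48 unit-months. Unit 1 is open for 21 months and unit 2 for 19, giving 40 open and 8 control unit-months. Assumed: even accrual, 534/48 = 11.125 patients per unit-month, and a linear approximation on the model's linear-predictor scale.

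**Quantity.** The loading is the coefficient that Thrive receives when its true effect is zero and the only real difference is unit 1 minus unit 2. A loading of 1 means the whole unit difference is reported as a Thrive effect.

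**(a) Exposure = the unit's assigned status, no unit term, teams absent or crossing both units.** The unit indicator is balanced over months, so loading = [(21 - 19)/2] / (residual sum of squares of the Thrive indicator after the time terms).
- No time term: 48 × (40/48) × (8/48) = 6.667; 1/6.667 = 0.15. Check: 21/40 - 3/8 = 0.15.
- Linear month: 6.667 - 79²/2300 = 3.953; 1/3.953 = 0.25. (79 is the cross-product of Thrive with centred month; 2300 is the sum of squares of month.)
- Categorical time: only the two months of enrollment period 1 contribute, 0.5 each; 1/1 = 1.00.

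**(b) As (a) with categorical time, but k random team intercepts nested in each unit.** Loading = 1 / [1 + n₀ρ/((1 - ρ)k)], where n₀ = 22 × 11.125 = 244.75 patients per unit outside enrollment period 1 and ρ is the assumed team ICC.

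| ICC | 1 team per unit | 4 teams per unit |
|---|---|---|
| 0.001 | 0.80 | 0.94 |
| 0.01 | 0.29 | 0.62 |
| 0.05 | 0.07 | 0.24 |
| 0.10 | 0.04 | 0.13 |

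Fixed team effects nested in units give 0.

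**(c) Exposure = individual participation, as Variables and Measures states; categorical time, no unit term.** Control unit-months supply 8 × 11.125 = 89 usual-care patients. The other 267 - 89 = 178 must be non-participants in open units. Open months hold 40 × 11.125 = 445 patients, so average uptake is 267/445 = 60%. With uptake u₁ and u₂ in the two units, the 4 unit-months of enrollment period 1 and the 38 later ones give:

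loading = [4(u₁/4) + 38(u₁ - u₂)/4] / [4(u₁/2)(1 - u₁/2) + 38ū(1 - ū)], with ū = (u₁ + u₂)/2.

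| u₁ / u₂ | Calculation | Loading |
|---|---|---|
| 60% / 60% | 0.6 / 9.96 | 0.06 |
| 70% / 50% | 2.6 / 10.03 | 0.26 |
| 50% / 70% | -1.4 / 9.87 | -0.14 |
| 80% / 40% | 4.6 / 10.08 | 0.46 |
| 40% / 80% | -3.4 / 9.76 | -0.35 |

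**Illustration.** Suppose the units' rates were 0.30 and 0.25, a ratio of 1.20. The spurious Thrive rate ratio is 1.20 raised to the loading: 1.20 under (a) with categorical time, 1.20^0.06 = 1.01 under (c) with equal uptake, and 1.20^0.46 = 1.09 or 1.20^-0.35 = 0.94 at the unequal extremes.

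**With a fixed unit effect.** The loading is 0 in every scenario. The variance cost is:
- Assigned status, categorical time: the variance multiplies by 1 + 2/22 = 1.09 (0.0899 to 0.0981).
- Participation, equal uptake: 9.96 / (9.96 - 0.6²/12) = 1.003, so under 1%.
- Participation, 40%/80%: 9.76 / (9.76 - 3.4²/12) = 1.11. At 80%/40%: 10.08 / (10.08 - 4.6²/12) = 1.21. The cost is larger where the bias removed is larger.

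**The case against.** A reader might infer that any unit difference passes in full into the Thrive effect. The document does not support this, for three reasons.

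First, full loading needs the unit's assigned status as exposure. The article makes participation the exposure, so much of the contrast may lie within units, and at equal uptake the loading falls to about 0.06.

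Second, full loading also needs categorical time and teams that work across both units, and neither is stated. Nested teams would absorb some or all of the unit difference. Variables and Measures lists type of unit and discharging team as separate items, but that does not show that teams cross units; a team nested in a unit could be listed in the same way.

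Third, no bias can be set against a planned detectable difference between Thrive and usual care, because Power Analysis states none.

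It can also be said that one sentence in a journal article is not a full model specification. Type of unit is among the data collected, and the complete list of terms may be in a document not shown. This stands so far: the article does not state that unit is excluded. It does not remove the point, because the article is not silent on clustering. It names the factors accounted for, and the randomised one is not among them.

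**Conclusion.** The point holds as a should-fix mismatch between design and stated model: the unit is randomised, and the primary model names team and time only. Bias from a unit difference is possible, but neither its size nor its sign can be fixed from the article. The loading is 0.15 to 1.00 for assigned-status exposure when team does not absorb the unit difference. It is 0.04 to 0.94 with nested random teams (ICC 0.001 to 0.10, 1 to 4 teams per unit), and 0 with fixed nested teams. For participation it is about 0.06 at equal uptake and -0.35 to +0.46 over the unequal uptakes tried. These values rest on even accrual, the linear approximation and, for participation, average uptake of about 60%. The size of any real unit difference is unknown; the 1.20 ratio is only an illustration.

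**What to change.** Add hospital unit to the primary model as a two-level fixed effect alongside the time effects. Keep medical team as the random effect, and state whether teams are nested in units or work across both. Do not rely on a random unit effect, because two levels barely identify a variance.

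This is one line of specification using unit-level data of the kind the protocol already plans to collect, and Results places the analysis in early 2026. The statistical price is about 1% or less more variance (participation, equal uptake) to 9% (assigned status), and more if uptake differs sharply between units. A unit term does not settle whether exposure should be assigned condition or participation, and does not remove confounding by who participates; that needs its own decision.

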### Power Analysis

Based on a power analysis, a sample size of 472 (236 Thrive participants and 236 usual care) for the outcome of readmissions, or a sample of 534 (267 Thrive participants and 267 usual care) for the outcome of ED visits, will yield 80% power to detect significance at the *P*<.05 level. Our goal is a sample size of 534 to ensure adequate power for both outcomes. This assumes a 20% (106/534) loss to follow-up rate. Furthermore, assuming at least a third of the patients will have SMI and an overall 30-day readmission rate of 28% (44/160), a sample of 534 patients will have 80% power to detect an odds ratio as small as 1.46, comparing those with and without SMI, to be statistically significant at the *P*<.05 level. Power analyses were conducted using Power Analysis and Sample Size 2021 (NCSS Statistical Software) [28].

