### Strengths and Limitations

The major strength of our study is the use of a stepped-wedge, cluster randomized controlled trial design. This allows all eligible patients at our study hospital the opportunity to be referred to Thrive during the study window. One limitation is the use of EHR data for our usual care group, as we can only capture use that occurs within our health system.

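### The 80% power statement gives no Thrive effect size and makes no stated allowance for the two-unit, 8-week stepped wedge or the time-adjusted model; under that model power is far lower

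*Protocol article*

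**What the plan says.** The Power Analysis section gives "a sample size of 472 (236 Thrive participants and 236 usual care) for the outcome of readmissions" and "a sample of 534 (267 Thrive participants and 267 usual care) for the outcome of ED visits", and says these "will yield 80% power to detect significance at the" 5% level. It adopts 534 as the goal and adds "This assumes a 20% (106/534) loss to follow-up rate". It does not mention clusters, steps, correlation within units or adjustment for time, and it names no difference between Thrive and usual care. A 28% readmission rate appears, but only for the comparison of patients with and without SMI.

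The Design and Randomization section describes two units, one per sequence: "Eight weeks later, the second unit will begin Thrive referrals". Table 1 sets out 3 months of baseline, two enrolment periods of 2 months each, and 17 months of follow-up. The first unit is on Thrive from enrolment period 1 and the second from enrolment period 2.

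The Aim-2 Analysis section specifies a mixed-effects negative binomial model "accounting for both medical team and time effects". The form of the time term is not given. The Strengths and Limitations section says: "The major strength of our study is the use of a stepped-wedge, cluster randomized controlled trial design".

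**The concern.** Two equal groups with an allowance for drop-out look like a calculation for independent patients, and the trial described is different. In Table 1 both units are on usual care for 3 months, they differ for 2 months, and both are on Thrive for the remaining 19. Once calendar time is in the model, only the 2-month window compares Thrive with usual care at the same time. The rest of the information contrasts earlier patients with later ones.

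If the time-adjusted model is fitted as planned, the result is likely to be imprecise, and a null finding could be read as evidence against Thrive. If time is handled loosely, a result reported as randomised is in substance a before-after comparison.

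**Working it through.** **The plan's own figure.** Neither 472 nor 534 can be reproduced, because no Thrive effect size is stated. The nearest candidate is the pilot's 50% reduction (Introduction, Background), which the Power Analysis section does not cite. Applied to 28%, a two-sided 5% test of 28% against 14% needs [1.96·√(2·0.21·0.79) + 0.8416·√(0.28·0.72 + 0.14·0.86)]² / 0.14² = 132 per group, or 132/0.8 = 165 after 20% loss. The plan has 236. Conversely, 80% power corresponds to 28% against 17.2% with 236 evaluable per group, or 28% against 16.1% with 189 (236 less 20%).

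**Inputs for the check.** The schedule is Table 1: 2 units by 24 months, with eight weeks taken as 2 months. The total is N = 534. My assumptions are a two-sided test, a normal approximation, even accrual, controls from pre-step unit-periods only, a fixed unit effect and no further intra-unit correlation. To avoid assuming rates, the effect is set so that 267 against 267 independent patients gives exactly 80% power, a standardised value of 1.96 + 0.84 = 2.80.

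**Formula.** Let R be the variance of the Thrive effect under a given model divided by its variance with 267 against 267 and no adjustment. Then power = Φ(2.80/√R − 1.96) + Φ(−2.80/√R − 1.96).

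**No time term.** Control is 3 + 5 = 8 of 48 unit-months, so even accrual gives 89 control and 445 Thrive patients. R = (1/4)/[(1/6)(5/6)] = 1.80 and power is 55%.

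**Unit plus categorical period.** After removing period means, Thrive status varies only in the 2-month window, which is 2/24 = 1/12 of the data. Removing the unit effect leaves a fraction (1/12)(11/12) of the two-group information.
- R = 144/11 = 13.09 (13.18 if patients are forced to 267/267).
- 2.80/√13.09 = 0.774, and Φ(−1.186) + Φ(−2.734) = 12%.

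**Unit plus linear calendar month.** Weighted least squares over the unit-by-month cells gives R = 3.08 to 3.10. Then 2.80/√3.10 = 1.59 and power is 36%.

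**Sensitivity.**

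| Change of assumption | Categorical | Linear month |
|---|---|---|
| As above | 12% | 36% |
| Recruitment ends after enrolment period 2, N still 534 | 24% | 32% |
| Effect is 28% to 14%, N = 427 to 534 | 17-20% | 53-63% |
| 10% of post-step patients are concurrent usual-care controls | 39% | 56% |
| 25% | 63% | 71% |
| 40% | 72% | 77% |

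- In the second row the window is 2/7 of the data, so R = 1/[(2/7)(5/7)] = 4.9 for categorical time.
- In the third row, at N = 534, the standardised effect is 0.14·√267/√0.322 = 4.03. For categorical time 4.03/√13.09 = 1.11 and power is 20%.
- Coding linear time by period index gives about 15-16%, and by period midpoint about 21-25%.
- Omitting the unit effect moves the categorical figure only from 12.1% to 12.8%.

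**The case against.** The strongest reply is that 12% and 36% are not fixed by the document. That is right, for four reasons.

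- **Effect size.** None is stated, so the effect is calibrated. For that effect some loss of power is built in, and the finding is the size of the loss.
- **Controls.** Variables and Measures defines exposure as participation in Thrive and draws usual care from the EHR without limiting it to pre-step periods. Concurrent non-participants may therefore be intended. Power is then 39-77% for the calibrated effect. With a fall from 28% to 14% it could pass 80%: with 25% concurrent controls and categorical time R is 1.50, 4.03/√1.50 = 3.29, and power is about 91%. But this compares patients who took up Thrive with patients who did not, which is not the randomised contrast.
- **Time.** The form of the time term may properly be left to an analysis plan.
- **Recruitment.** Table 1 labels only two periods as enrolment. If recruitment stopped there, control to Thrive is 8:6 unit-months, close to 1:1, and the 89:445 split does not apply.

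Some stronger readings are tempting. A reader might infer that the calculation is shown to be one for two independent groups. That is a fair inference from the equal split and the silence on design, but the document does not say it, and the figures cannot be reproduced to prove it. A reader might note that two units allow only two orders, so a randomisation test could not reach significance, or might scale the detectable risk difference until it exceeds the base rate. Neither bears on the plan, which uses model-based inference on counts. Finally, the Strengths section praises the design because every eligible patient can be offered referral. It makes no power claim.

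**Conclusion.** The point stands in conditional form. The 80% statement has no stated effect size and no visible link to the two-unit wedge or to the time-adjusted primary model. With pre-step controls, every time-adjusted scenario examined falls below 80%. For the calibrated effect, power is about 12% (categorical period) or 36% (linear month) on the full Table 1 schedule, and 24% or 32% if recruitment ended early. For a fall from 28% to 14% on the full schedule it is 17-20% or 53-63%. These figures assume no variation between unit-periods beyond the model terms; any such variation would lower them further. They illustrate the size of the problem and are not the trial's established power. This is not a detail that could be left to an analysis plan, because the article itself states the power figure and it does not match the design and model stated beside it.

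**What to change.** 1. State the assumed Thrive-versus-usual-care effect for readmissions and for ED visits.
2. State which patients form the control set (pre-step unit-periods only, or also concurrent non-participants) and the form of the time term.
3. Replace the 80% statement with the power or detectable effect under the planned mixed model and the Table 1 schedule, and say whether recruitment continues through the 17 months.
4. State that most of the Thrive-versus-usual-care information is before-after, so that the result is not presented as a mainly randomised comparison.

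This costs wording and one recalculation. The disadvantage is a much less favourable power figure.

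A longer retrospective EHR baseline is optional. With even accrual and the calibrated effect, linear-time power is about 41% with 15 baseline months (534·36/24 = 801 patients) and about 53% with 27 (534·48/24 = 1,068). The gain comes only from the added usual-care records: with the total held at 534, power falls to about 29-30%. It also relies on a parametric time trend and does not restore 80% for that effect.

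### The power paragraph does not say whether 534 is before or after the 20% loss, and the SMI claim (80% power for an odds ratio of 1.46) fails on its own inputs under either reading

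*Protocol article*

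**What the plan says.** All the figures stand in one paragraph of the protocol article (Aim-2 Methods, Power Analysis).

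- Readmissions: "a sample size of 472 (236 Thrive participants and 236 usual care) for the outcome of readmissions".
- ED visits: "a sample of 534 (267 Thrive participants and 267 usual care) for the outcome of ED visits, will yield 80% power".
- Target: "Our goal is a sample size of 534 to ensure adequate power for both outcomes".
- Loss: "This assumes a 20% (106/534) loss to follow-up rate".
- SMI comparison: "assuming at least a third of the patients will have SMI and an overall 30-day readmission rate of 28% (44/160), a sample of 534 patients" is said to give 80% power for an odds ratio as small as 1.46 between patients with and without SMI.

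The paragraph gives the significance level as 0.05 without saying whether the test is one- or two-sided. It gives no base rate or effect size for Thrive against usual care on either outcome. The number left after loss, 428, does not appear.

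**The concern.** The same number, 534, carries an 80% power statement, serves as the goal, and is the denominator from which 106 patients are removed. A reader cannot tell whether each 80% refers to patients enrolled or patients analysed. If the former, the loss is already allowed for. If the latter, the goal has no allowance for a loss that the paragraph itself assumes.

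The SMI sentence is the only power statement printed with enough inputs to recompute, and those inputs do not give 80% at either number. At stake is what may be claimed once 534 is reached. The trial would be described as adequately powered for readmissions, ED visits and the SMI comparison. For the third that is not so, and for the first two it depends on an unstated choice. A null SMI result would then be read with more confidence than it deserves.

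**Working it through.** **Inputs.** All come from the Power Analysis section: 472 (236 per arm), 534 (267 per arm), loss 106/534, SMI share one third, overall 30-day readmission rate 28% (44/160 = 27.5%), odds ratio 1.46, significance level 0.05, power 80%. Two-sided testing is my assumption; one-sided results are also shown. Clustering and time effects are ignored throughout.

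**1. Number left after loss.** 534 − 106 = 428, or 214 per arm.

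**2. Thrive against usual care, if 472 and 534 are analysed numbers.** Power scales as Φ((1.960 + 0.842) × √(n/N) − 1.960).

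- ED visits: Φ(2.802 × √(428/534) − 1.960) = Φ(0.548) = 0.71.
- Readmissions: Φ(2.802 × √(428/472) − 1.960) = Φ(0.708) = 0.76.
- Keeping 534 analysed would need 534/0.8 = 667.5, so 668 enrolled.

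**3. Thrive against usual care, if the totals already include loss.** 427/0.8 = 533.75, which rounds up to 534, and 377/0.8 = 471.25, which rounds up to 472. The totals therefore fit an inflated number. The per-arm 236 does not: 188/0.8 = 235, and 189/0.8 = 236.25, which rounds up to 237. Rounding does not settle the question. With no design effect printed, neither 80% can be recomputed.

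**4. SMI comparison as printed.** The two group rates must satisfy (2/3)p₀ + (1/3)p₁ = 0.28 and an odds ratio of 1.46. This gives p₀ = 25.4% without SMI and p₁ = 33.2% with SMI, a difference of 0.0780. Power = Φ((|p₁ − p₀| − z × SE₀)/SE₁), where SE₀ uses the pooled variance and SE₁ the unpooled variance.

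- N = 534 (356 and 178): SE₀ = 0.0412, SE₁ = 0.0422. (0.0780 − 1.960 × 0.0412)/0.0422 = −0.065, so power is 47%.
- N = 428 (about 285 and 143): SE₀ = 0.0460, SE₁ = 0.0471. (0.0780 − 1.960 × 0.0460)/0.0471 = −0.259, so power is 40%.

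The printed 80% is not reproduced. Solving the same formula for 80% power gives the detectable odds ratio, and about 1,187 analysed patients would be needed for 1.46.

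| Reading of 1.46 (one third SMI) | Power at 534 | Power at 428 |
|---|---|---|
| Odds ratio, overall 28%, two-sided | 47% | 40% |
| Odds ratio, overall 28%, one-sided | 60% | 52% |
| Risk ratio, overall 28%, two-sided | 77% | 67% |
| Risk ratio, 28% in the non-SMI group, two-sided | 85% | 76% |

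| Two-sided, overall 28%, one third SMI | 534 | 428 |
|---|---|---|
| Odds ratio detectable at 80% power | 1.75 | 1.87 |

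Using 27.5% in place of 28% leaves the odds-ratio power at 47% and 40%. Raising the SMI share to 40% or 50% gives at most 50% at 534, two-sided.

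**The case against.** The strongest reply is that the ordinary reading contains no contradiction. The loss is expressed as a share of the goal, so 534 is most naturally the enrolled number with loss built in, and the totals fit that. This stands. The 71% and 76% are conditional on the other reading and cannot be presented as the trial's actual power.

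A reader might go further and infer that at least one printed 80% must really be about 71%. The documents do not support that. The ED and readmission figures may be correct on the ordinary reading, and the SMI figure recomputes to 47% or 40%, not 71%. Scaling 1.46 to 428 patients, which gives about 1.53, is not sound either, because it takes as correct an 80% that the inputs do not give.

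A reader might also note that 1.46 comes near 80% at 534 when taken as a risk ratio, and conclude that the SMI sentence used the full 534. That too is unsupported. The text says odds ratio. Moreover, a risk ratio of 1.46 reaches about 80% at 428 if 28% is the non-SMI rate and half the patients have SMI, and 85% at 428 with one third SMI and a one-sided test. The figure cannot show which number was used.

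The objection does not rescue the SMI sentence. Reaching 80% at 428 means replacing the stated odds ratio with a risk ratio and also changing the reference rate and SMI share, or using a one-sided test.

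Nor is this detail that an article would leave to a fuller document: the sample size, loss, effect and power are all printed here.

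**Conclusion.** The point holds in two parts of different strength.

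- **Enrolled or analysed.** The paragraph is ambiguous. A shortfall in the Thrive comparisons, to about 71% for ED visits and 76% for readmissions, exists only if 534 and 472 are analysed numbers. Otherwise those figures may stand and cannot be tested.
- **SMI comparison.** The stated 80% is not delivered under either reading. On the printed inputs it is about 33 percentage points too high at 534 (80 − 47) and 40 points too high at 428 (80 − 40).

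The second part rests on a two-sided 5% test of two proportions, 28% taken as the overall rate as stated, one third SMI, and no adjustment for clustering or time. One-sided testing lifts power only to 60% at 534 and 52% at 428. This should be corrected; it does not call the design into question.

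**What to change.** State what 534 is. Either label it as the number enrolled and 428 (214 per arm) as the number analysed, or, if outcomes are taken from the EHR for every included patient so that nobody is dropped, delete the loss assumption and call 534 the analysed number. The Data Collection and Sources section takes outcomes from the EHR, while Strengths and Limitations notes that only use within the health system is captured, so the text should also say what loss means here.

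Then restate the power figures at the analysed number, with the effect size, base rate and sidedness behind the readmission and ED figures. Replace the SMI statement with its recomputed power for 1.46, or with the detectable odds ratio: about 1.87 at 428 or 1.75 at 534. If 1.46 was meant as a risk ratio, say so, say which group the 28% describes, and recompute.

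The cost is one paragraph of wording and a few recalculated figures. No extra enrolment is required. The stated power or detectable effect becomes less favourable, most clearly for the SMI comparison.

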### Aims and Hypotheses

The specific aims of this research are to engage staff and community advisors in participatory processes to (1) prioritize additional components to the current Thrive care model suitable for participants with co-occurring SMI and evaluate the context required for adaptation of the intervention; (2) examine utilization outcomes (ie, Thrive referral; readmission; and ED, primary, and specialty care visits) for Medicaid-insured individuals with and without SMI who receive Thrive compared with usual care—we hypothesize that individuals with SMI who receive usual care will have worse utilization outcomes compared with those without SMI and that all individuals receiving Thrive with and without SMI will have better outcomes compared with those with usual care; and (3) evaluate the acceptability, appropriateness, feasibility, and cost-benefit of an adapted Thrive clinical pathway that is tailored for Medicaid-insured patients with co-occurring SMI.

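### The stated 80% power for an SMI odds ratio of 1.46 is wrong: the plan's own inputs give about 47%, and the detectable odds ratio is about 1.75

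*Protocol article*

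**What the plan says.** The Power Analysis section first sets sample sizes for the Thrive versus usual care comparison: 472 for readmissions and 534 for ED visits, with 534 as the goal. On attrition it adds: "This assumes a 20% (106/534) loss to follow-up rate".

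It then makes a separate statement about SMI status. "assuming at least a third of the patients will have SMI", and with an overall 30-day readmission rate of 28% (given as 44/160), it claims that "a sample of 534 patients will have 80% power to detect an odds ratio as small as 1.46, comparing those with and without SMI" at the .05 level. It does not say whether the test is one- or two-sided.

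In Aims and Hypotheses, the hypothesis that compares patients by SMI status is placed within usual care: "individuals with SMI who receive usual care will have worse utilization outcomes compared with those without SMI".

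**The concern.** The sentence gives every input needed to check it except sidedness, and the result looks too good. With 534 patients split 1:2 and a 28% event rate, an odds ratio of 1.46 is a difference of about 8 percentage points, which is small for a sample of this size.

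This is the only power figure in the article for any SMI comparison, in a trial whose title and aims centre on SMI. A non-significant SMI comparison would be read against it as evidence that no disparity of 1.46 or more exists. If true power is below one half, the trial would miss such a disparity more often than it found it. A null result is a realistic prospect: in the Introduction, the pilot of Thrive participants found no statistically significant difference by SMI status in readmissions or ED use.

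**Working it through.** **Inputs (all from Power Analysis unless noted)**

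- N = 534. One third with SMI gives n1 = 178 (SMI) and n0 = 356 (no SMI).
- Overall readmission rate 0.28 (44/160 = 0.275, rounded up).
- Odds ratio 1.46, alpha 0.05, claimed power 80%.
- Two-sided testing is an assumption here. One-sided is tried below.

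**Step 1: group rates implied by the odds ratio.** Solve (2/3)·p0 + (1/3)·p1 = 0.28 with [p1/(1−p1)] / [p0/(1−p0)] = 1.46. This gives p0 = 0.254 and p1 = 0.332, a difference of 0.078.

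**Step 2: power at 1.46 (attempt to reproduce 80%).** Two-proportion z test with pooled variance under the null:

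- SE0 = √[0.28 × 0.72 × (1/356 + 1/178)] = 0.0412
- SE1 = √[0.254 × 0.746/356 + 0.332 × 0.668/178] = 0.0422
- z = (0.0780 − 1.96 × 0.0412) / 0.0422 = −0.065
- Power = Φ(−0.065) = **47.4%**

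A Wald test of the log odds ratio gives 47.2%, and simulation with 200,000 runs gives 47.3%. The stated 80% is not reproduced.

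**Step 3: odds ratio detectable with 80% power.** Solving the same formula for power 0.80 gives an odds ratio of **1.75** (24.1% against 35.8%, risk ratio 1.48). Simulated power at 1.75 is 79.9%.

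**Step 4: sample size for 80% power at 1.46.** About 1,185 patients. The Hsieh formula for logistic regression with a binary covariate gives the same number.

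**Step 5: other readings of the sentence.**

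| Reading (odds ratio 1.46) | Power |
|---|---|
| Main case | 47.4% |
| Rate 27.5% instead of 28% | 47.0% |
| 28% taken as the non-SMI rate | 49.2% |
| 28% taken as the SMI rate | 43.6% |
| Half the patients with SMI | 49.8% |
| One-sided 0.05 | 59.6% |
| One-sided, half SMI, 28% as non-SMI rate | 65.2% |
| N = 668 (534/0.8, if 534 were the number left after loss) | 56.1% |

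The most favourable combination at N = 668 reaches 73.6%. No reading of 1.46 as an odds ratio for SMI status comes within 2 points of 80%.

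**Step 6: loss to follow-up and the usual-care hypothesis.** The same method with smaller N, keeping 28% and one third with SMI:

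| Patients | Power at 1.46 | Detectable odds ratio at 80% |
|---|---|---|
| 534 | 47% | 1.75 |
| 428 (534 less 106) | 40% | 1.87 |
| 267 (usual care only) | 27% | 2.20 |
| 214 (usual care, less 20%) | 23% | 2.41 |

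**Step 7: could 1.46 be another effect measure?** Read as a risk ratio at N = 534, 1.46 gives 76.7% power (28% overall) or 84.6% (28% as the non-SMI rate). The risk ratios detectable at 80% are 1.48 and 1.43. The value 1.46 falls between them.

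Two other readings also come near the claim. A one-sided Poisson rate ratio of 1.46 has 79.1% power. The Hsieh formula for a continuous covariate with R² = 0.5 gives a detectable odds ratio of 1.465 (two-sided, N = 534). The text states neither reading.

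**The case against.** The strongest reply is that the number may be right and the label wrong. Read as a risk ratio, 1.46 has 77% to 85% power, so the power claim would be roughly sound before loss and the only error would be the word "odds". The document cannot settle which it is. This stands as a possible explanation of the error but does not clear the sentence. The text says odds ratio, and a reader will use it as one. If 1.46 is a risk ratio with 28% overall, the rates are 24.3% and 35.4%, and the matching odds ratio is (0.354/0.646)/(0.243/0.757) = 1.71.

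Second, sidedness and the software procedure are not given, and an article condenses. That is true, and two-sidedness is an assumption here, but a one-sided test reaches only 60%.

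Third, the usual-care figures go beyond what the power sentence claims, since it does not limit itself to that arm. They also apply the overall 28% to usual care. If 28% averages two equal arms and Thrive halves readmission, as the pilot reported, the usual-care rate x satisfies (x + 0.5x)/2 = 0.28, so x = 37.3%. The detectable odds ratios are then 2.10 (267 patients) and 2.29 (214), not 2.20 and 2.41. This is a fair caution: those figures are conditional and secondary. They stay well above 1.46 either way.

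Last, the sentence does not set the sample size, since 534 comes from the ED outcome. This is correct. It limits the consequence to how the SMI comparison is interpreted.

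**Conclusion.** The concern holds. On the plan's own inputs, with two-sided testing assumed, 534 patients give 47% power at an odds ratio of 1.46, not 80%, and the odds ratio detectable with 80% power is about 1.75. The gap of more than 30 points is too large to come from rounding or the choice of test. If 20% of the 534 are lost, the figures are 40% and 1.87. Within usual care, where the SMI hypothesis sits, they are about 27% and 2.2 (23% and 2.4 after loss), provided the 28% rate and one-third SMI share apply in that arm.

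None of these figures allows for clustering. The finding does not touch the 472 and 534 targets for the Thrive comparison. A mislabelled risk ratio is plausible but cannot be confirmed from the document.

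**What to change.** Check the software output for the effect measure actually used, then replace the sentence. Suggested wording: *With 534 patients (428 evaluable after 20% loss), one third with SMI and an overall 30-day readmission rate of 28%, the odds ratio for SMI versus no SMI detectable with 80% power at two-sided 0.05 is about 1.75 (1.87 evaluable). Within the usual-care group alone, assuming the same rate and SMI share, it is about 2.2 (2.4 evaluable).*

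If 1.46 is a risk ratio, say so, state which group the 28% refers to, and give the matching odds ratio. Also state which population the 44/160 describes, because the usual-care figures depend on it.

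The cost is one corrected sentence and a less favourable statement of sensitivity. Design, sample size and analysis are unchanged, and no additional patients are needed. The correction should be made before the analysis planned for early 2026.
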